### Allocation of intervention

First, the buildings will be matched into similar pairs based on geographic location, numbers of units within the building, proportion of units occupied by seniors, existing EMS call rate (number of calls/100 apartment units) in the 2 years prior to the intervention period and the types of social programmes offered to residents. Then, for each matched pair, one building will be randomised to receive the intervention and the other will not receive the intervention (control group). Block randomisation will be used with random allocation of the intervention within each block of two buildings.

Residents of the intervention buildings will have access to the CHAP-EMS programme, in additional to their usual medical care and wellness programmes, while residents of control buildings will only have access to their usual medical care and wellness programmes. Since randomisation is occurring at the building-level, it is not expected that providing usual care as the control condition will impact study recruitment, results or interpretation.

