### Sample size

Given that our main outcome will be rates of calls per 100 residents per year, we calculated our sample size using the formula for the Poisson test. Based on data from the Hamilton Paramedic Services, the average rate of calls for our pilot sample was 44.06 EMS calls per year per 100 residents older than 65 years. If we assume a difference of 10% (a difference of 4.4 EMS calls per 100 residents per year) between the intervention and control groups, with 0.8 β and α of 0.05, we would need a sample of 131 per group. This is a conservative estimate of effect size since the pilot study showed a 25% reduction in EMS calls.^26^ Also, a difference of 10% is considered operationally significant by Hamilton Paramedic Services (personal communication with [name]). This is likely to be significant in other Ontario localities as well.

The overall sample size will be a minimum of 700 participants per arm (intervention or control) in 12 or more intervention buildings across all sites. Considering the Design Effect (cluster sampling by buildings), we can accommodate an intracluster correlation coefficient (ICC) of up to 2.5% given our proposed sample size. There is no literature regarding an ICC for a similar study.

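### The stated ICC tolerance of 2.5% does not follow from the plan's own figures, and the base of 131 per group beneath it is far too small for a 10% reduction at any ICC

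*Protocol article*

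**What the plan says.** All the figures stand in the Sample size section of the protocol article. The method is described as follows: "we calculated our sample size using the formula for the Poisson test". The control rate is "44.06 EMS calls per year per 100 residents older than 65 years", the assumed effect is a 10% reduction (4.4 calls), and the error rates are given as "with 0.8 β and α of 0.05". The result is "we would need a sample of 131 per group".

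The section then sets a minimum of 700 participants per arm in at least 12 intervention buildings, names the building as the cluster for the design effect, and concludes that "we can accommodate an intracluster correlation coefficient (ICC) of up to 2.5% given our proposed sample size". It adds: "There is no literature regarding an ICC for a similar study". It prints neither a cluster size nor a design-effect calculation.

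Under Allocation of intervention, buildings are to be paired on several characteristics, among them "existing EMS call rate (number of calls/100 apartment units) in the 2 years prior to the intervention period". One building of each pair is then randomised to the programme, so the arms have equal numbers of buildings.

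**The concern.** The section prints every input needed to check the 2.5%, and the check fails. The statement also carries a promise: that 700 per arm keeps the planned power for a 10% reduction in call rate as long as the ICC stays at or below 2.5%. That promise depends on 131 being the right size without clustering. If 131 is too small, the tolerance is not merely misprinted; the trial lacks the stated power whatever the ICC. A null result on the call rate could then be read as evidence against a 10% reduction, the size the plan calls operationally significant, when the trial had little chance of detecting one.

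**Working it through.** **Inputs.** From Sample size: 131 per group, 700 per arm, 12 buildings per arm, 0.4406 calls per resident-year, 10% reduction (to 0.39654), α 0.05. From Study design: one year of programme, so one person-year per resident. Assumed: the printed 0.8 β means 80% power, and the test is two-sided unless stated.

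**1. The plan's 2.5%.** With design effect DE = 1 + (m − 1) × ICC, the tolerable ICC is (N/n − 1)/(m − 1).

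- m = 700/12 = 58.3
- Allowable DE = 700/131 = 5.344
- Tolerable ICC = 4.344/57.33 = 0.0758, or **7.6%**

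At ICC 2.5% the design effect is 1 + 57.33 × 0.025 = 2.433, and 131 × 2.433 = 319 per arm would do.

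Variants that do not recover 2.5%:

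| Variant | Tolerable ICC |
|---|---|
| 5% loss to follow-up (665 per arm) | 7.5% |
| 16 buildings per arm | 10.2% |
| 262 (both groups) as base, 700 as N, 12 buildings | 2.9% |
| Unequal building sizes, CV 0.5 | 6.0% |
| Unequal building sizes, CV 1.0 | 3.8% |

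A CV of about 1.4 in building size would be needed to bring 7.6% down to 2.5%. Solving for the cluster size instead gives m = 4.344/0.025 + 1 = 174.7, and 700/174.7 = 4.0 clusters per arm. As a check, 131 × (1 + 174 × 0.025) = 701.

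**2. The base size.** The two-sample Poisson size is n = (z_α + z_power)² × (λ₁ + λ₂)/(λ₁ − λ₂)².

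- λ₁ + λ₂ = 0.4406 + 0.39654 = 0.83714
- (λ₁ − λ₂)² = 0.04406² = 0.0019413
- Two-sided: 7.849 × 0.83714/0.0019413 = **3,385 per arm**
- One-sided: 6.183 × 0.83714/0.0019413 = **2,666 per arm**

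Two-sample Poisson variants (pooled, square-root and log-rate forms, one- and two-sided) at 80% power for a 10% reduction run from 2,664 to 3,397. One-sample forms give 1,332 to 1,786, and a comparison of two proportions gives 1,554 to 1,973. None gives 131, and all exceed 700. For 700 per arm to suffice without clustering, the control rate would have to be 7.849 × 1.9/(0.01 × 700) = 2.13 calls per resident-year, nearly five times the stated rate.

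**3. Tolerable ICC on the corrected base.**

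- 10% reduction: 700/3,385 = 0.21, below 1, so no ICC of zero or more is tolerable. One-sided, 700/2,666 = 0.26, with the same conclusion.
- 25% reduction (the pilot result): λ₂ = 0.33045, n = 7.849 × 0.77105/0.11015² = 499, and the tolerable ICC is (700/498.8 − 1)/57.33 = **0.7%**. One-sided, n = 393 and the tolerable ICC is 1.4%.

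**4. Power and detectable reduction at 700 per arm in 12 buildings, two-sided.** The effective size is 700/DE. Power is Φ(difference/SE − 1.96), with SE = √((λ₁ + λ₂)/effective size). For 10% at ICC 0: SE = √(0.83714/700) = 0.0346, 0.04406/0.0346 = 1.274, and Φ(−0.686) = 0.246. The last column solves the formula in step 2 for the reduction at the effective size.

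| ICC | Effective size | Power, 10% reduction | Power, 25% reduction | Reduction detectable with 80% power |
|---|---|---|---|---|
| 0 | 700 | 25% | 91% | 21% |
| 1% | 445 | 17% | 75% | 26% |
| 2.5% | 288 | 13% | 57% | 32% |
| 7.6% | 131 | 8% | 30% | 46% |

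**The case against.** **The mismatch is on the safe side.** If 131 were right, a design that tolerates 7.6% also tolerates 2.5%, and more than 12 buildings would only widen the margin. This stands: the inconsistency between 2.5% and 7.6% costs no power by itself. A reader might infer that it does; the loss comes entirely from the 131.

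**The larger figures rest on readings of the text.** The printed 0.8 β could be taken literally as 20% power. The two-sample size would then be 539 two-sided (tolerable ICC about 0.5%) or 278 one-sided (about 2.6%), so some tolerance would exist. But neither size is 131, and a trial planned for 20% power would not be a sensible design. Sidedness is not stated, but a one-sided test leads to the same conclusion.

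**700 and 12 are minimums.** True, and the call-rate denominator is all residents aged 55 or older, so the analysed number could be larger. It would still have to reach 3,385/12 = 282 per building in 12 buildings, even at ICC 0.

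**Matching and baseline data help.** Pairing on prior call rate and the pre-intervention data can reduce between-building variance, so the clustering allowance is not the only protection for power. They do not reduce the Poisson variance that produces the 3,385.

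**The cause of the error.** Because 2.5% fits four clusters per arm and the abstract speaks of four communities, a reader might infer that communities were used as clusters. The documents do not support this. The Sample size section names buildings as the cluster, Study design lists five regions, and a leftover from some other design would fit as well. The reason is unknown.

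**The missing ICC.** A reader might also infer that the plan overlooked an ICC it already had. It says only that the literature offers none, and it describes the collection of prior call rates as a future step. Nothing shows that those data were held when the size was set.

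**Conclusion.** The concern holds as a wrong stated property of the design. The 2.5% does not follow from 131, 700 and 12 buildings, which give 7.6%; that part alone is a cautious inconsistency. The material error is the base of 131. At 80% power the stated rate and effect need about 3,385 per arm two-sided (2,666 one-sided), so 700 per arm cannot give the stated power for a 10% reduction at any ICC.

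The conclusion assumes that 80% power was meant, one person-year per resident, Poisson variation within buildings, equal building sizes and a normal approximation. It also uses the plan's rate for residents over 65 as the rate for the trial population. As step 2 of the working shows, no plausible change in that rate would rescue the 131.

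**What to change.** In the Sample size section:

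1. Delete the statement that an ICC of up to 2.5% can be accommodated.
2. Replace 131 with a base size from a stated two-sample formula, giving sidedness and writing power as power.
3. Recompute the design effect with the building as the cluster (about 58 residents at 700 per arm in 12 buildings).
4. Restate power for a 10% reduction, and the reduction detectable with 80% power, for 700 per arm in 12 buildings over a stated range of ICCs, as in the last table of the working.
5. Inform that range by the between-building, within-pair variation in the pre-intervention call rates to be collected for matching. Those rates are per 100 apartment units, while the outcome is calls by residents aged 55 or older per 100 such residents. They must therefore be put on the outcome's basis, and Poisson noise removed, before they measure the variance that is needed.

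The cost is a short calculation, the conversion of the matching data once collected, and less favourable stated figures. The randomisation and data collection need not change.

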### Recruitment process

Recruitment of intervention building residents into the CHAP-EMS programme will be organised in a multifaceted way. Existing building-based wellness groups and Tenants’ Associations will identify leaders from among the residents of the buildings who can champion the CHAP-EMS programme. The programme will also be advertised to the target population using posters in the intervention buildings. Posters will be translated into other languages as needed by the population composition in the buildings chosen.

Participants in the control buildings will receive usual care and will not be recruited for any intervention. The only contact the researchers will have with the participants of the control buildings will be to obtain survey responses regarding their health perceptions and behaviours at the beginning and end of the study. They will not be informed of the CHAP-EMS programme occurring in the matched intervention building.

### Research intervention

The intervention includes BP, diabetes and fall risk assessments, health education/promotion, targeted referral to appropriate in-house wellness sessions and community resources, identification and referral of high-risk patients to their family physician, as well as regular communication of participants’ health information to their physician. The sessions will be held weekly in a common area of the intervention apartment buildings and will be implemented by paramedics from the local paramedic service who have undergone a structured training programme (3–4 h of online, interactive training modules, including case studies and the observation of an intervention session led by another paramedic) to assure intervention fidelity.

Individual participants will voluntarily attend and will complete the informed consent process with a paramedic on their first visit (see online supplementary appendix B). Following consent, they will have their risk factors assessed and entered into a database, and they will be advised to make lifestyle changes (if applicable) with the help of available community resources and educational pamphlets. Participants with a moderate-to-high score on CANRISK will be asked to return for a fasting blood glucose capillary test, where the paramedic will guide the participant through pricking his or her own finger with a lancet and applying a drop of blood to a test strip to measure fasting blood sugar. CANRISK assessments will be repeated at 6-month intervals to assess change.

Using a prespecified algorithm, participants will be directed to appropriate services. Those identified as high risk will be immediately referred to appropriate healthcare resources, such as their primary healthcare provider. Based on a moderate risk profile and a needs assessment, participants will be referred to community resources to assist them in managing their health, specifically targeting the four common risk factors for chronic disease identified by the WHO (physical inactivity, unhealthy diet, tobacco use and harmful use of alcohol),^3^ as well as mental health and stress. These community resources are run by Community Housing and Public Health and include age-appropriate physical activities, speakers on healthy eating, social engagement opportunities with cooking demonstrations and referrals to local community resources, as required. Follow-up for identified concerns will be provided through linkages with primary healthcare providers and CCAC referrals.

Consenting participants will have their BP and risk profile sent by fax from the CHAP-EMS database to their primary healthcare provider. Participants without a family physician will be referred to CCAC for assistance with locating a suitable physician.

### Primary and secondary outcome measures

The primary outcome of EMS call rate (number of calls for building made by residents aged 55 years or older per 100 residents aged 55 years or older in the subsidised seniors’ building) will be available for each building from the EMS administrative database. The primary outcomes of change in measured systolic and diastolic BP, and difference in 10-year diabetes risk (CANRISK score), will be available from the measurements entered by the paramedics into the study database. The secondary outcomes will be difference in health perceptions, behaviours, intentions regarding behaviours, health literacy and knowledge of resources, measured by interviewer-led survey preintervention and postintervention; and difference in health-seeking behaviour (eg, number of ED visits/population 55 years and older), which will be based on administrative databases.

### Process evaluation measures

Process evaluation of CHAP-EMS will include participation rates (number of participants attending, initial attendance and repeat visits), programme delivery (eg, completion of risk assessments) and other programme evaluation measures (eg, detection rates for hypertension and diabetes).

### Data gathering procedures

Rates of EMS calls, ED visits, primary care visits and other healthcare utilisation will be collected from the administrative database of the local paramedic services, hospital ED databases, Institute for Clinical Evaluative Sciences (ICES) databases, the CHAP-EMS database and consenting participants’ primary care charts. Administrative data will be collected preintervention and postintervention, and retrospectively for the 12 months of intervention.

Health perceptions, behaviours and intentions regarding behaviours, health literacy and knowledge of resources related to chronic disease risk factors will be collected from consenting participants using an interviewer-led survey called the Health Awareness and Behaviour Tool (HABiT). This questionnaire covers the following domains: demographics, health status and quality of life, knowledge and risk factors (cardiovascular and diabetes), health utilisation and access to healthcare, and perceived concern and understanding of risk. It was developed by the research team, loosely based on existing validated questions. It has been pretested, piloted and validated in a sample of older adults in Ontario. Each item will be assigned a score and participant questionnaire results will be summarised as numerical scores. These outcomes will be analysed at the individual level and linked to administrative databases.

There will be two periods of data collection with the HABiT survey: a preintervention survey for residents of the intervention and control buildings administered up to 3 months prior to the intervention, and a postintervention survey administered up to 3 months immediately postintervention. Residents will be notified about the surveys through presentations at tenant engagement meetings, word-of-mouth and posters within the buildings. Surveys will be administered by trained college/university students and research assistants.

Physical measures (eg, BP, weight), risk assessment scores and process outcomes will be collected through the CHAP-EMS electronic database. The database is encrypted, and only accessible to the research team and the paramedics implementing the study.

Any urgent medical concerns identified or similar adverse events will be handled following protocol (eg, phoning the primary physician or EMS, depending on the level of urgency); these events will be recorded and reported to the ethics committee where appropriate.

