### Secondary questions

Will there be a *difference in the health perceptions, behaviours, intentions regarding behaviours, health literacy and knowledge of resources* in senior residents living in subsidised seniors’ housing after receiving the CHAP-EMS programme compared to their own baseline measurement, and compared to seniors in a building not receiving the programme?*Will there be a difference in health-seeking behaviour (eg, number of hospital emergency room visits and primary care visits)* by senior residents living in subsidised seniors’ housing compared to baseline, and compared to seniors in a building not receiving the programme?

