## Methods and analysis

### Study design

This study is designed as a pragmatic clustered randomised controlled trial with parallel intervention and control groups. The trial will occur in the Hamilton, York, Guelph, Sudbury and Simcoe regions of Ontario, Canada; a current list of participating regions can be found on clinicaltrials.gov under trial number NCT02152891(see online supplementary appendix A). Within each region, up to eight buildings will be selected and paired based on their characteristics. Within each pair, one building will be randomly allocated to receive the intervention and the other building will act as its control. The programme will be delivered for 1 year in the intervention buildings. Outcomes will be analysed using parallel comparisons (of intervention vs control buildings) as well as preintervention and postintervention comparisons. Process evaluation will be carried out after the 1 year study implementation and will assess the programme implementation in terms of efficiency of the processes in its delivery, participation rates, compliance and ways of improving it. All operations will be overseen by the research team at the Department of Family Medicine, McMaster University, with advice from local stakeholders (eg, public health). Local EMS will monitor the intervention session staffing on a day-to-day basis.

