### Control of bias

For the primary outcome of EMS call rate, we will collect at least 1 year of data before the intervention starts and also use a parallel design (for pairwise analysis) to examine the possible effect of seasonality. For the HABiT, participants will not be informed about the group comparisons. Surveys will be anonymous to decrease the possibility of social desirability bias.

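### The two HABiT survey windows fall in adjacent calendar quarters, so the planned own-baseline comparison cannot separate a programme effect from a seasonal or secular shift

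*Protocol article*

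**What the plan says.** All references are to the protocol article.

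- **Timing.** Under Data gathering procedures, "There will be two periods of data collection with the HABiT survey": one "administered up to 3 months prior to the intervention, and a postintervention survey administered up to 3 months immediately postintervention". Residents of both intervention and control buildings are surveyed. Study design fixes the length of the programme: "The programme will be delivered for 1 year in the intervention buildings".
- **Comparisons.** Under Secondary questions, the survey outcomes after the programme are to be "compared to their own baseline measurement, and compared to seniors in a building not receiving the programme". Study design says the same of outcomes in general: parallel comparisons "as well as preintervention and postintervention comparisons".
- **Season.** Under Control of bias, the article will collect at least a year of earlier data and "use a parallel design (for pairwise analysis) to examine the possible effect of seasonality", but it says this for the EMS call rate. For HABiT, the same section mentions only that participants are not told of the group comparisons and that surveys are anonymous.
- **Analysis.** Data analysis plans GEE on a numerical HABiT score and a Bonferroni adjustment for secondary analyses.

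**The concern.** A follow-up survey exactly one year after baseline would meet each respondent at the same time of year. Here one window ends at the start date and the other opens at its anniversary, so the follow-up round as a whole comes later in the year than the baseline round. HABiT covers health behaviours and health status, and the programme targets physical inactivity and diet, which could plausibly vary with season in Ontario.

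With only two rounds, the survey data within one arm cannot tell season from programme. The intervention arm could show an apparent gain with no programme effect, or a real gain could be hidden. The Discussion expects better health behaviour and sees policy implications in such findings, so a within-arm change read as a programme effect could be put to use.

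**Working it through.** The article states no figure for this point, so there is none to reproduce. The check is calendar arithmetic, followed by an illustration under stated assumptions.

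**Inputs from the article** (months from programme start): pre-survey window −3 to 0; programme 0 to 12; post-survey window 12 to 15.

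**1. Overlap.** Modulo 12 months, the post window 12 to 15 becomes 0 to 3. The pre window is −3 to 0. They meet at one point, the start date and its anniversary, and otherwise share no dates. This holds for every start date. A start on 1 April gives a January–March baseline and an April–June follow-up.

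**2. Interval between surveys.**
- Shortest: 12 − 0 = 12 months, a calendar offset of 0.
- Longest: 15 − (−3) = 18 months, an offset of 6 months.
- Between midpoints: 13.5 − (−1.5) = 15 months, an offset of 3 months.

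**3. Spread of the offset.** Assume survey dates are uniform and independent within each window; the article gives no distribution. The offset is then triangular on 0 to 6 months, with P(offset < d) = d²/18 for d ≤ 3.

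| Offset | Share of respondents |
|---|---|
| under 1 month | 1/18 = 5.6% |
| under 1.5 months | 2.25/18 = 12.5% |
| 1.5 to 4.5 months | 75% |
| over 4.5 months | 12.5% (by symmetry) |

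With fixed 3-month seasons, all respondents move to the next season if the start date lies on a season boundary. If it lies mid-season, about 50% do, with about 25% in the same season and 25% two seasons on.

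**4. Shift in the mean score.** Assume a yearly sinusoid of amplitude A in the score.
- Averaging over a 3-month window multiplies the amplitude by sin(π/4)/(π/4) = 0.900.
- Two window midpoints 3 months apart differ by at most 2·sin(π/4) = 1.414 times that amplitude.
- Largest shift: 0.900 × 1.414 × A = 1.27A.
- Mean absolute shift over start dates: 1.27A × 2/π = 0.81A.
- Smallest shift: 0, when the two windows lie symmetrically about a seasonal peak or trough.

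**5. What the control arm does.** Write the mean change in the intervention arm as programme effect + S, and in the control arm as S, where S is the seasonal and secular shift common to both. The own-baseline contrast estimates programme effect + S. The between-arm difference in change estimates (programme effect + S) − S = programme effect. The data for the second contrast are already planned.

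**The case against.** The strongest reply is that the plan already holds the remedy. Control buildings are surveyed in the same two rounds, the secondary questions ask for the comparison with them, and a shift common to both arms cancels there. What remains is an uncontrolled contrast on a secondary outcome, open to secular trend and regression to the mean as any before-after contrast is. A baseline before the programme and a follow-up after it is also a defensible choice. All of this stands, and it limits the point. It does not remove it, because the own-baseline comparison is posed as a question to be answered, not as a description.

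Four stronger readings are tempting, and the article does not support them.

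- *Every own-baseline comparison sets one season against the next.* The windows are maxima. A respondent seen just before the start and just after the end is compared about 12 months apart, with almost no offset. The own-baseline comparisons of blood pressure and CANRISK use measurements from the sessions, not these windows.
- *The between-arm comparison is biased too.* That would need survey timing within the windows to differ by arm. Nothing in the article suggests it does, and fieldwork scheduling is commonly left to a fuller document.
- *A false-positive rate can be quoted.* Taking A = 0.10 SD, 400 paired respondents, a pre-post correlation of 0.6 and a design effect of 1 + (700/12 − 1) × 0.025 = 2.43, the standard error is √(2 × 0.4 × 2.43/400) = 0.070. A null programme would then reach p < 0.05 in about 45% of trials at the worst start date (81% if clustering is ignored). Averaged over start dates, it is 25%; at an illustrative Bonferroni level of 0.01, 11%. With A = 0.05 SD, the last two become 10% and 3%. The amplitude, the number of pairs and the correlation are all assumed, so this range shows sensitivity and is not an estimate. Start dates that differ between regions would partly average the shift out.
- *HABiT scores are known to be seasonal.* The article does not say so, and the score also covers knowledge, access to care and perceptions.

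**Conclusion.** The point holds for the own-baseline HABiT comparison only. That the two windows share no dates follows from the article's own timings and needs no assumption. The average offset of 3 months assumes evenly filled windows, and the shift of 0 to 1.27A assumes a sinusoidal season. The amplitude A is unknown and may be small, so the bias has no established size or direction. It is nevertheless built into the schedule, two rounds cannot identify it within one arm, and a multiplicity adjustment does not remove it. This is a matter of which contrast may carry a conclusion, not an error that threatens the trial's primary outcomes.

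**What to change.** In Secondary questions and Data analysis, state that HABiT conclusions about the programme rest on the between-arm difference in pre-to-post change. Report within-arm change from own baseline descriptively, without a test of programme effect. Where feasible, survey both buildings of a matched pair over the same weeks in each round, so that a common shift cancels as fully as possible.

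The cost is that the within-arm result no longer counts as evidence of effect, plus minor survey scheduling. No respondents are added, because control buildings are already surveyed in both rounds. Moving the follow-up survey into the last 3 months of the programme year would align the calendar months, but some residents would then answer before a full year of exposure. That is a trade-off and is not recommended here.
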